## Abstract

**Background:**

Fluid removal during dialysis, also known as ultrafiltration (UF), leads to intradialytic hypotension (IDH) in a significant number of patients treated with hemodialysis (HD) and is associated with an increase in morbidity and mortality. At present, there are no accepted standards of practice for the prevention or treatment of IDH. Relative blood volume monitoring (BVM) is based on the concept that the hematocrit increases with UF, relative to the patient’s baseline hematocrit. The use of BVM biofeedback, whereby the HD machine automatically adjusts the rate of UF based on the relative blood volume, has been proposed for the prevention of IDH.

**Methods/Design:**

This is a 22-week randomized crossover trial. Participants undergo a 4-week run-in phase to standardize medications and dialysis prescriptions. Subsequently, participants are randomized to standard HD or to BVM biofeedback for a period of 8 weeks followed by a 2-week washout phase before crossing over. The dialysis prescription remains identical for both arms. The primary outcome is the frequency of symptomatic IDH as defined by an abrupt drop in the systolic blood pressure of ≥20 mm Hg accompanied by headache, dizziness, loss of consciousness, thirst, dyspnea, angina, muscle cramps or vomiting. Secondary outcomes include the number of symptomatic IDH episodes and any reduction in IDH episodes, nursing interventions, dialysis adequacy, total body water, extra- and intracellular fluid volumes, brain natriuretic peptide and cardiac troponin levels, blood pressure, antihypertensive medication use, patient symptoms and quality of life.

**Discussion:**

Our study will determine the impact of using BVM biofeedback to prevent IDH and other serious adverse events in susceptible patients.

**Trial registration:**

Clinicaltrials.gov NCT01988181 (6 November 2013).

**Electronic supplementary material:**

The online version of this article (doi:10.1186/1745-6215-15-483) contains supplementary material, which is available to authorized users.

## Background

The majority of patients with end-stage renal disease are treated with hemodialysis (HD) to regulate their fluid balance and other native kidney functions [1, 2]. Patients treated with HD have a 5-year mortality rate of 57%, with the majority of deaths due to cardiac and infectious causes [3, 4]. A growing body of literature has emerged linking chronic fluid overload in HD to hypertension, left ventricular hypertrophy and increased all-cause mortality [5–7]. To prevent volume overload and maintain fluid balance, 1 to 5 L of fluid must be removed during each HD treatment.

Rapid fluid removal, or ultrafiltration (UF), during a short period of time can lead to intradialytic hypotension (IDH) in as many as 25% to 50% of patients treated with HD [8]. IDH is most commonly defined as an abrupt drop in systolic blood pressure of ≥20 mm Hg accompanied by symptoms of cerebral, cardiac, gastrointestinal or musculoskeletal ischemia [9–11]. Observational studies have shown that IDH or a drop in post-dialysis systolic blood pressure is associated with an increase in morbidity and mortality [12–20].

UF during HD leads to a fall in the patient’s blood volume. The blood volume can be measured by tracking the changes in hemoglobin or protein concentration at the arterial port during dialysis using optical photometry or ultrasound [21–28]. In clinical studies, higher rates of UF lead to faster declines in the relative blood volume and as a result, a steeper decline in the blood volume monitoring (BVM) curves [27–29]. BVM-guided biofeedback is based on the principle that the relative blood volume (compared to baseline) appears to decrease more rapidly in sessions complicated by IDH [25, 30]. As a result, BVM-guided UF biofeedback, whereby the dialysis machine automatically reduces the rate of UF prior to reaching the patient’s critical blood volume, has been proposed for the prevention of IDH and its sequelae [22, 23, 31–34].

We will conduct a randomized controlled clinical trial to test whether biofeedback incorporating BVM-guided UF adjustments alone (without adjustment of the dialysate sodium concentration), in addition to best clinical practice, results in a reduction in the frequency of symptomatic IDH episodes and patient symptoms compared to best clinical practice alone. Secondary outcomes include the frequency of IDH-related interventions, dialysis-related symptoms, dialysis adequacy, volume control, biomarkers of volume overload and cardiac stress, blood pressure and quality of life.

## Methods/Design

### Study design

This is a 22-week parallel-group randomized crossover trial. During the first part of the study, the run-in and dialysis optimization phase, eligible participants will undergo a 4-week run-in. During this period, all participants will undergo a comprehensive clinical assessment including a clinical weight assessment, an antihypertensive medication review and standardization of their dialysis prescription. At the end of the run-in phase, participants that still meet the eligibility criteria will enter part 2, the randomized crossover phase. In this phase, the participants are randomized to regular best clinical practice HD (without BVM-guided UF biofeedback; the control arm) or to best clinical practice plus BVM-guided UF biofeedback (the intervention arm) for an 8-week period. This will be followed by a 2-week washout phase and then the participants will be crossed over for a second 8-week phase. The participant flow chart and timeline are shown in Figure 1. The study will be conducted and reported following the Consolidated Standards of Reporting Trials (CONSORT) 2010 guidelines [35]. The study protocol was approved by the University of Calgary Conjoint Health Research Ethics Board (ethics ID: REB13-1139).

**Figure 1 Fig1:**
[figure not shown]
**Participant flow diagram.** HD, hemodialysis; IDH, intradialytic hypotension.

### Study setting

The clinical trial will be held at two tertiary care units (Foothills Medical Centre and Peter Lougheed Centre) and three community HD units (Fanning Centre, Sheldon Chumir Centre and Sunridge Centre) in the Southern Alberta Renal Program, Calgary, Alberta, Canada.

### Study participants

All participants who have been treated with HD for more than 3 months will be screened for eligibility. To be eligible for the study, participants must be >18 years of age, medically stable, undergo HD three to four times per week for a minimum of 3 hours per session, and have had >30% of their HD sessions in the preceding 8 weeks complicated by symptomatic IDH. Participants with serum sodium ≤133 mmol/L [36], hemoglobin <80 g/L, active malignancy, a history of blood transfusion or hospitalization in the preceding 4 weeks, routine use of diuretics for volume management, a history of ongoing urine output estimated at greater than or equal to 250 mL (one cup) per day, or a planned change in the renal replacement modality during the study period will be excluded. Informed consent will be obtained from each individual who agrees to participate in the study.

### Definition of symptomatic intradialytic hypotension

Symptomatic IDH is defined as a drop in systolic blood pressure of ≥20 mm Hg from baseline with associated symptoms [9, 10]. Symptoms include sudden-onset headache, dizziness, unconsciousness, thirst, dyspnea, angina, muscle cramps and vomiting [10, 11].

### Interventions

#### Part 1: run-in phase

Following enrollment, participants will undergo a 4-week run-in phase to optimize their dialysis weight and dialysis prescriptions, and to determine the critical relative blood volume values (BVM will be enabled). During the first 2 weeks of the run-in phase, participants will undergo a medication review and dry-weight reduction based on a modified protocol from the Dry-Weight Reduction In Hypertensive Hemodialysis Patient (DRIP) trial [37, 38].

#### Part 2: crossover study phase

Participants that continue to have more than 30% of their sessions complicated by symptomatic IDH during the run-in phase are randomized to either 8 weeks of best clinical practice (without BVM or biofeedback; control) or best clinical practice plus BVM-guided UF biofeedback (intervention), followed by a 2-week washout period (using the control phase HD prescription) before crossing over to the other study arm for a second 8-week block. Participants will have clinical assessments of their dry weight at the beginning of each week.

#### Control group

All study participants will be dialyzed with the Fresenius 5008 HD machine (Fresenius Medical Care, Bad Homburg, Germany) using high-flux dialyzers. Participants in the best clinical practice (control) group will use the same prescription used during the run-in phase: dialysate sodium of 138 mmol/L, dialysate calcium of 1.25 mmol/L, dialysate temperature of 36°C and constant UF rate. BVM will be disabled in this group.

#### Intervention group

Participants in the BVM-guided UF biofeedback group will have the same prescription as the control group, but will also have the UF rate automatically adjusted by the Fresenius 5008 HD machine based on changes in relative blood volume.

### Ultrafiltration biofeedback guided by blood volume monitoring using the Fresenius 5008

The Fresenius 5008 uses an ultrasound monitor incorporated into the machine to detect ultrasonic velocity changes to derive the total protein concentration, which is a sum of total plasma proteins and hemoglobin. A temperature monitor is also incorporated to correct for temperature-related changes in ultrasound velocity [21, 39]. Since the total protein does not change, any changes in its concentration are attributed to blood volume changes (Figure 2). The relative blood volume is calculated by dividing the initial concentration of total protein by the total protein concentration at any given time, multiplied by 100 [21]. This method for measuring relative blood volume has been previously validated with both optical and laboratory hemoglobin techniques [21, 24].

**Figure 2 Fig2:**
[figure not shown]
**Depiction of blood volume monitoring (BVM) profile and the corresponding ultrafiltration profile.**

The HD software in the Fresenius 5008 HD machine adjusts the UF rate based on the critical blood volume entered at the beginning of the dialysis session for each individual patient. There is no adjustment to the dialysate sodium concentration. To determine the actual UF rate, the HD software first calculates the maximum UF rate. The maximum UF rate is 2 times the total UF divided by the remaining time. The actual UF rate is the maximum UF rate multiplied by the UF coefficient, which is a number between zero and one. To allow for the maximum UF at the onset of HD, the UF coefficient is one at the start of HD and continues to remain at one until the relative blood volume is halfway towards the critical relative blood volume. At the halfway point between the start and the critical relative blood volume, the UF coefficient decreases linearly. Once the critical relative blood volume is reached, the UF coefficient becomes zero, resulting in cessation of UF [21, 24, 40].

### Determination of critical blood volume

There is currently no standardized method for determining the critical relative blood volume. To standardize this process, a single investigator (KL) will use the following method/algorithm:Identify the most recent episode of symptomatic IDH as per the study definition.The critical blood volume will be equal to the relative blood volume recorded immediately prior to the episode of symptomatic IDH.The critical blood volume will be reassessed weekly.

### Weight adjustments

Each week participants will have their target weight assessed by a single study investigator (KL). The rounding dialysis physician will be encouraged to discuss any weight adjustments with study personnel.

### Responding to episodes of intradialytic hypotension

In the event that an IDH episode occurs, the bedside dialysis nurse will follow a predefined IDH algorithm (Additional file 1) [38]. Following resolution of an IDH episode as defined in the primary outcome section, UF will resume. In the control group, a constant UF rate will be reset to meet the UF goal. In the intervention group, BVM-guided UF biofeedback will be re-enabled.

### Outcomes

#### Primary outcome

The primary outcome is the rate of symptomatic IDH. The number of symptomatic IDH episodes along with the duration of each dialysis treatment will be captured. The rate of IDH for each session will be calculated by dividing the number of episodes by the duration of the session in hours. The rate of IDH will be calculated for every dialysis treatment. The rate of symptomatic IDH will be measured in the 2 months preceding enrolment and during each phase of the study. By using the rate of symptomatic IDH, rather than the frequency or number of IDH episodes per session as done in previous studies, we will be more sensitive to meaningful changes in IDH episodes as multiple episodes of symptomatic IDH can occur over various durations of dialysis [31, 32, 41].

#### Secondary outcomes

The secondary outcomes of interest are the number and frequency of nursing interventions, the number and frequency of both symptomatic and asymptomatic IDH, the number and frequency of dialysis symptoms, dialysis adequacy as measured by single-session *Kt*/*V*, total body water, extracellular fluid volume (ECFV), intracellular fluid volume (ICFV), the ECFV:ICFV ratio as determined by electrical bioimpedance, changes in brain natriuretic peptide (BNP) level, changes in high-sensitivity-cardiac troponin level, changes in blood pressure (mean arterial pressure pre-, intra- and post-dialysis), changes in antihypertensive medications, changes in the BVM curves, intradialytic and interdialytic symptom survey, and nursing satisfaction.

IDH-related nursing interventions are defined as the use of the Trendelenburg/supine position, discontinuation of UF, fluid/saline challenge, return of blood, shortened dialysis run, or a prolonged (more than 15 minutes) post-dialysis recovery period as a result of IDH or its symptoms. Given the subjective nature of IDH-related symptoms and intervention, in-services and customized dialysis run sheets will be provided to all nurses at participating dialysis centers to ensure that all events are recorded, and recorded consistently.

Dialysis adequacy, measured by single-pool *Kt*/*V*, will be measured and recorded (usual care) at the end of each dialysis session on the session sheet. Single-pool *Kt*/*V* will be calculated using the previously validated, online clearance measurement method, which detects changes in conductivity in the dialysate to reflect the clearance of serum electrolytes and urea [42].

Whole body and segmental bioimpedance analysis has been validated for the determination of fluid composition in HD patients [43–47]. Electrical bioimpedance will be performed during the mid-week HD session of weeks 1, 4, 8, 12, 14, 18 and 22 of the study to determine the total body water, ECFV and ICFV levels and the ECFV:ICFV ratio.

Biomarkers of cardiac stress, serum BNP and high-sensitivity cardiac troponin levels as well as the number and class of antihypertensive medications used will be recorded at the mid-week HD session of weeks 1, 4, 12, 14 and 22 of the study. Diuretic use will not be recorded as participants with significant residual renal function are excluded.

Two types of survey will be administered and completed by the patient alone, or with the aid of the dialysis nurse. The first, provided at the beginning of each dialysis session, is a validated survey inquiring about the time it took the patient to recover to baseline following a previous dialysis session (interdialytic period) [48]. The second, provided at the end of each dialysis session, inquires about intradialytic symptoms of IDH, specifically nausea, vomiting, chest pain, shortness of breath, headache, muscle cramps, dizziness, fainting, fatigue and anxiety. A survey inquiring about nursing perception and attitudes of the BVM-guided UF biofeedback will be provided to the nurses at the end of the control and intervention phases.

### Sample size calculation

We have previously estimated that 23% of our HD population have IDH [38]. To estimate the sample size, we conservatively assumed that only one IDH episode would occur per run (although it is likely that more than one episode will occur per run, increasing the study power). With this approach, and using a 2 × 2 crossover design, we estimated that a sample size of 30 participants would provide a power of 90% to demonstrate a 30% reduction in the rate of IDH under the biofeedback treatment vs. the control treatment, with a two-sided alpha of 0.05. We will enroll 34 participants to guard against dropout, which can be as high as 30% [41]. These estimates are based on simulation studies assuming only one IDH episode per run and two Poisson processes with average rates of IDH equal to 7 (control) and 5 (intervention) episodes over 24 runs. We used R (R Foundation for Statistical Computing, Vienna, Austria) [49] for simulations, and the package clusterPower in R.

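### Sizing on one IDH episode per run is called conservative, but repeat episodes raise power only under conditions the plan does not state

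*Protocol article*

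**What the plan says.** Under Sample size calculation, the protocol article states that "a sample size of 30 participants would provide a power of 90" per cent. The stated aim is "to demonstrate a 30% reduction in the rate of IDH under the biofeedback treatment vs. the control treatment", tested two-sided at the 5% level. The figure comes from a simulation of "two Poisson processes with average rates of IDH equal to 7 (control) and 5 (intervention) episodes over 24 runs", in which each run was limited to a single episode. The one-episode assumption is presented as cautious: "we conservatively assumed that only one IDH episode would occur per run (although it is likely that more than one episode will occur per run," with the consequence that power goes up. No condition is attached.

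Under Primary outcome, the analysed quantity is the number of symptomatic episodes in a session divided by its duration in hours. The reason given for preferring this to earlier measures is that "multiple episodes of symptomatic IDH can occur over various durations of dialysis".

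Under Responding to episodes of intradialytic hypotension, ultrafiltration resumes in the same session once an episode has resolved. "In the control group, a constant UF rate will be reset to meet the UF goal", and in the intervention group biofeedback is switched on again.

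**The concern.** The power figure is derived for a count with at most one event per run, while the outcome to be analysed has no such cap. The only link between the two is the remark that repeats help. That remark treats each extra episode as fresh information. A second episode in a run that already had one comes from the same patient, with the same fluid to remove and the same session conditions, so it may say little that is new about the treatment.

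At stake is how a null result would be read. If 90% is taken as a floor, a null result looks like good evidence against a 30% reduction. If 90% is only one point in a range that depends on how repeats behave, that reading is too strong.

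**Working it through.** **Inputs from the protocol article.** N = 30 participants, each contributing to both treatments; 24 runs per phase; 7 (control) and 5 (intervention) per phase; two-sided alpha 0.05.

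**Assumed, because the article gives no figure.** The distribution of episodes per affected run, with mean m and coefficient of variation CV. For a geometric distribution, 1 + CV² = 2 − 1/m. Session lengths are taken as equal, and the test is of a rate ratio of 1.

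**Step 1: the plan's own figure.** For Poisson counts compared within participants:

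SE = √[(1/7 + 1/5)/30] = 0.107, and |ln(5/7)| = 0.336.

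Power = Φ(0.336/0.107 − 1.96) = 88.2%.

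With an exact 30% reduction (7 vs 4.9) it is 91.3%. Both lie within 2 points of 90%, so the stated figure reproduces.

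Strictly, at most one event per run makes the phase count binomial out of 24, not Poisson. Subtracting 1/24 from each variance term gives SE = √[(1/7 + 1/5 − 2/24)/30] = 0.093 and power 95.1%. The Poisson base therefore errs toward caution.

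**Step 2: clustered repeats, similar in both arms.** Hold affected runs at 7 and 5 and multiply each by the same m. The rate ratio is 5m/7m = 5/7, unchanged. The variance of the log ratio becomes

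[(1 + CV²)/7 + (1 + CV²)/5]/30, less (2/24)/30 on the binomial base.

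Apart from the binomial correction, information per arm is affected runs/(1 + CV²), which cannot exceed the number of affected runs. Power is unchanged if every affected run has the same number of episodes, and falls otherwise.

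| Mean episodes per affected run (geometric) | 1 + CV² | Power, Poisson base | Power, binomial base |
|---|---|---|---|
| 1 (no repeats) | 1.00 | 88% | 95% |
| 1.3 | 1.23 | 81% | 89% |
| 1.5 | 1.33 | 78% | 85% |
| 2.0 | 1.50 | 73% | 80% |

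Simulation (4,000 replicates, participant-level robust standard error) gave 76% and 71% on the Poisson base at means of 1.5 and 2.0, and 83% and 78% on the binomial base.

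**Step 3: cases where power holds up or rises.**

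- *Independent repeats.* If 7/24 and 5/24 are the chances of at least one episode and episodes within a run are Poisson, totals are −24 ln(1 − 7/24) = 8.28 and −24 ln(1 − 5/24) = 5.61. The ratio is 0.68 and power is 97%.
- *Mild repeats.* If 20% of affected runs have exactly two episodes, 1 + CV² = (1 + 3 × 0.2)/1.2² = 1.11. At 50% it is (1 + 3 × 0.5)/1.5² = 1.11 again. Power is 92% (binomial) or 85% (Poisson).
- *Per-run negative binomial*, common dispersion, 7/24 control runs affected, total rate ratio 5/7: 92%, 89% and 82% at means of 1.25, 1.5 and 2.0.
- *Biofeedback also trims repeats.* From 1.5 to 1.4 per affected run, the ratio is (5 × 1.4)/(7 × 1.5) = 0.667 and power is 91% (Poisson) or 96% (binomial). From 2.0 to 1.8 it is 93% or 96%.
- *Higher control rate.* With 9 affected control runs and the same ratio, power at means of 1.5 and 2.0 is 94% and 91% on the binomial base.

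**Step 4: where an apparent gain can come from.** In the clustered simulations at a mean of 1.5, a plain Poisson test that ignores clustering showed 91% to 93% power. Its type I error was 11% (binomial base) to 16% (Poisson base), so that gain is not real.

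**The case against.** The strongest reply has four parts.

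First, nothing is miscalculated: the 90% reproduces, and the whole loss comes from a repeat distribution that the article does not give. This stands. A reader might infer that the stated power is wrong or that the trial is underpowered, and the document supports neither.

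Second, equal repeats in both arms may be unrealistic. After an episode, control returns to a constant rate and the intervention arm returns to biofeedback, so the arms differ where repeats arise. The Primary outcome section also says that counting all episodes makes the measure more sensitive. This stands as a possibility, and Step 3 shows that a small reduction in repeats restores power. But the sizing section does not rest its claim on such an effect.

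Third, there is slack elsewhere. The Poisson variance exceeds the one-per-run binomial variance, and entry requires more than 30% of sessions affected (30% of 24 is 7.2), so the control rate may exceed 7. This also stands, though rates may drift back toward the mean after selection.

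Fourth, the Statistical analysis section provides a negative binomial model for over-dispersion. That is meant to protect the type I error; it does not restore power.

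Two further readings go too far. One is that power falls under every form of clustering: constant repeats leave it unchanged, and the negative binomial at means of 1.25 and 1.5 stays at or above the Poisson 88%. The other is that the trial was sized on a wholly different endpoint: the section speaks of a rate and of episodes, and only the cap of one per run sets it apart.

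**Conclusion.** The point holds in a limited form. The article states without condition that repeats raise power, and the design does not have that property. The direction depends on whether repeats are close to independent within a run and on whether biofeedback reduces them, and the plan states neither.

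Under equal geometric repeats averaging 1.3 to 2.0 per affected run, the loss is about 6 to 15 points on either base (95% to 89–80%, or 88% to 81–73%). These figures illustrate an assumption and are not an estimate for this trial. In particular, 73% to 89% should not replace 90%: it would join the low end of one base to the high end of the other and leave out the favourable cases. What can be said is that 90% is conditional on no within-run clustering and is not a lower bound.

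**What to change.** - In Sample size calculation, delete the word that calls the one-episode assumption conservative and the clause saying that repeats increase power.
- Re-run the simulation on total episodes with a stated distribution of episodes per affected run. Take it from the 8 weeks before enrolment or from pooled run-in data, both of which the plan already collects. Include scenarios with equal repeats in both arms and with fewer repeats under biofeedback.
- Report 90% as conditional on no within-run clustering, with the simulated range beside it.
- Report the number of runs with at least one symptomatic episode as a supporting analysis of the primary outcome, since that matches the capped count used for sizing.

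Keep the sample size. The cost is one re-run of an existing R simulation, a few changed sentences and one extra analysis of data already recorded. The stated power may look less favourable in some scenarios.

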### Recruitment

Recruitment will take place sequentially at the four participating HD units. From pilot data, we anticipate that approximately 20% of the 400 HD patients in participating units will meet the criteria for IDH [38] and at least half of the eligible participants (40 participants) will be willing to participate in our study [50, 51].

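### Enrolling 34 covers about 12% loss, not the dropout of up to 30% named in the same sentence, and the plan does not say clearly whether the 34 are counted before or after the run-in

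*Protocol article*

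**What the plan says.** The protocol article, Sample size calculation, states that 30 participants in a 2 × 2 crossover "would provide a power of 90% to demonstrate a 30% reduction in the rate of IDH", "with a two-sided alpha of 0.05". The basis is a simulation of two Poisson processes averaging 7 (control) and 5 (intervention) episodes over 24 runs. The section continues: "We will enroll 34 participants to guard against dropout, which can be as high as 30" percent. It gives no lower planning rate for dropout.

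Three other sections bear on what the 34 refers to:

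- Part 1: run-in phase: "Following enrollment, participants will undergo a 4-week run-in phase". Enrolment therefore comes first.
- Part 2: crossover study phase sets a second filter: "Participants that continue to have more than 30% of their sessions complicated by symptomatic IDH during the run-in phase are randomized". The Study design section likewise admits to Part 2 only those who remain eligible at the end of the run-in.
- Assignment of intervention: the allocation envelope is handed over once consent and enrolment are complete, with no mention of the run-in in between.

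The Recruitment section expects that "at least half of the eligible participants (40 participants) will be willing to participate".

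**The concern.** The number needed, the loss rate and the inflated number are stated next to each other, so they should agree. A reader will take the sentence to mean that the trial keeps 30 participants, and so 90% power, even if dropout reaches 30%. It does not.

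The count also has an unclear starting point. If the 34 are counted at enrolment, a margin of four people has to cover run-in exclusions as well as dropout after randomisation. At stake is the reliability of the stated power. The effect estimate, the test and the endpoint are not affected.

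**Working it through.** **Inputs, all from Sample size calculation:** 30 participants needed; 34 enrolled; dropout up to 30%; 7 vs 5 episodes per 24 runs; two-sided alpha 0.05; crossover. The simulated rates give a ratio of 5/7 = 0.714. An exact 30% reduction from 7 is 4.9, so both are shown.

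**1. Reproduce the stated power.** In a crossover with Poisson counts the participant effect cancels, so for n participants with both periods

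SE(log rate ratio) = √(1/(7n) + 1/(5n)), power = Φ(ln(7/5)/SE − 1.96).

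For n = 30: SE = √(1/210 + 1/150) = 0.1069; ln(7/5) = 0.3365; 0.3365/0.1069 = 3.147; power = Φ(1.187) = 88.2%. With 4.9 in place of 5 it is 91.3%. Both are within two points of the stated 90%, so the formula is a fair stand-in for the plan's simulation.

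**2. Check the step from 30 to 34.**

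- Largest loss that leaves 30: (34 − 30)/34 = 11.8%.
- Left after 30% loss: 34 × 0.70 = 23.8, i.e. 23 to 24.
- Needed to keep 30 at 30% loss: 30/(1 − 0.30) = 42.9, i.e. 43. The incorrect short cut 30 × 1.30 gives 39, which is also not 34.

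**3. Power at the cited loss, counting completers only.**

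| Completers | 7 vs 5 | 7 vs 4.9 |
|---|---|---|
| 34 | 91.8% | 94.2% |
| 30 | 88.2% | 91.3% |
| 24 | 80.4% | 84.3% |
| 23 | 78.7% | 82.7% |

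A Poisson simulation (20,000 replicates, between-participant log-SD 0 or 0.3, same test) agrees. With 24 completers it gives 80% to 81% (7 vs 5) and 84.5% (7 vs 4.9).

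**4. Run-in.** The document gives no exclusion rate. If the 34 are counted at enrolment, exclusions and dropout together may not exceed four people. Under assumed exclusion rates of 10%, 20% and 30%, the number randomised would be 34 × 0.9 = 30.6, 34 × 0.8 = 27.2 and 34 × 0.7 = 23.8, before any dropout.

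**The case against.** **The 30% is only a worst case.** It is an upper value taken from one cited crossover trial, not a forecast for this one. That is fair, but it is the only loss rate given and it is named as what the 34 guards against. If about 12% was the planning rate, the text should say so.

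**Partial data count.** The primary analysis is a mixed-effects Poisson model and leavers are censored, so someone lost late in the second period still informs both arms. This stands: the completer-only figures are somewhat pessimistic. Someone who leaves before crossing over, however, gives no within-person comparison, and the plan does not use this argument to justify 34.

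**Other model choices give more power.** The plan assumes at most one episode per run. Simulating that as binomial counts gives, with 24 completers, about 84% (Poisson test) or 88% (paired t-test) at 7 vs 5. At 7 vs 4.9 the paired t-test keeps about 91%. That one variant holds 90%, but it gives about 96% at n = 30 and so does not match the stated 90%. The plan also expects more than one episode in some runs, which it says raises power, but it does not quantify this.

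**The control rate may exceed 7.** Seven in 24 is 29% of runs at one episode each, just under the entry threshold of more than 30%. At an assumed 10 to 12 per 24, 24 completers would give about 92% to 97% by the same formula (ratio 5/7 or 0.70). This stands as a possibility, but the plan's stated power rests on 7.

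**A stronger reading.** A reader might infer that run-in exclusions and 30% dropout together leave a number in the teens, with power far below 80%. The document does not support that. It gives neither an exclusion rate nor a distribution of session rates. Pairing heavy run-in selection with a control rate of 7 is also inconsistent, because selection keeps those with more episodes. At 10 vs 7 with 18 completers, SE = √(1/180 + 1/126) = 0.1162 and power = Φ(0.3567/0.1162 − 1.96) = 87%. Over 10 to 12 per 24 and either ratio it is 83% to 92%.

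**Enrolment may mean randomisation.** The envelope wording allows this. It would remove the run-in part and leave 12% against 30% untouched.

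**Conclusion.** The mismatch is real and does not depend on any model: 34 protects 30 completers against 11.8% loss, not 30%. At 30% loss about 24 complete. On the plan's own rates power is then about 80% (7 vs 5) or 84% (7 vs 4.9), so the chance of missing the planned effect rises from the stated 10% to about 16% to 20%. This assumes Poisson counts, completers only and a control rate of 7 per 24. Partial data or a higher control rate would improve it.

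That run-in exclusions come out of the 34 is the likelier reading of the run-in sections, but not a certain one. It is a point to clarify, and its size cannot be worked out from the document.

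Two further inferences are not supported. The 90% at n = 30 is not wrong, since it reproduces. The 40 willing participants are not a ceiling, because the Recruitment section says at least half, although 43 does exceed that figure.

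This should be fixed, but it does not undermine the analysis.

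**What to change.** Replace the sentence on dropout with wording such as: *34 participants allow for about 12% loss; at 30% loss about 24 complete and power is about 80% to 84%.* Remove the implication that 34 guards against 30% dropout. State whether 34 counts participants enrolled before the run-in or randomised after it, and restate the expected number analysed and the power on that basis.

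The cost is rewording and a less favourable power statement. Raising the target to 43 randomised would protect 30 completers at 30% loss, but it exceeds the roughly 40 expected to be willing. Counting 34 at randomisation may also be hard to reach from that pool once run-in exclusions are taken off.
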